### Inclusion and follow-up

Participation starts after written informed consent. The women will be followed for 3 months when they collect samples and complete self-administered questionnaires (see Table 1). In order to motivate participants to complete follow-up, short text messaging (SMS) reminders are used, simple home-collection of samples is used [43, 44], and online questionnaires are used. Follow-up will entail 3 clinic visits, at weeks 4, 8, and 12. This last visit is also a routine STI clinic visit for repeat testing. Small incentives are provided (€10) at each follow-up clinic visit. Inclusion and follow-up visits are conducted by highly experienced nurses trained in STI care including motivational interviewing. Further, to increase the number of participants with complete follow-up data, the women who are included but who do not show up at week 4 for the clinic visit will be replaced by a new participant.

**Table 1 Tab1:** Overview of FemCure study time points at inclusion (pre-treatment) and during follow-up until 12 weeks post-treatment

	Pre-treatment	Week 1	Week 2	Week 4	Week 6	Week 8	Week 10	Week 12
	T0 (inclusion)	T1	T2	T3	T4	T5	T6	T7
Location	Clinic	Home	Home	Clinic	Home	Clinic	Home	Clinic
Number of anorectal samples collected per woman^a^	2	1	1	2	1	2	1	2
Number of genital samples collected per woman^a^	2	1	1	2	1	2	1	2
Number of pharyngeal swabs collected per woman^b^	2			1		1		1
NAAT on self-collected swabs	X	X	X	X	X	X	X	X
Viability testing on self-collected swabs	X			X		X		X
Chlamydia organism load, MLST^c^ and semen biomarker^c^ testing on self collected swabs	X	X	X	X	X	X	X	X
(Online) short questionnaire	X	X^d^	X	X	X	X	X	X

^a^Self-collected swabs

^b^Nurse taken swabs; stored for later testing

^c^In subset only

^d^Assessing treatment compliance and sexual behavior (in short) at week 1. At the other weeks, detailed self-reported sexual behaviors and symptoms are assessed

### Sample collection

Women will collect self-administered anorectal and vaginal swabs at 8 time-points at home and at the STI clinic (see Table 1) [43, 44]. A test-package with clear instructions is provided for self-collection at home. At clinic visits, the participants take an additional self-administered anorectal and vaginal swab that is stored in a different buffer and cooled immediately at −80 °C, to allow CT viability testing. Samples are sent in batches by courier to the laboratory for processing. Each clinic visit, also a pharyngeal nurse-taken swab is collected for later testing.

### Laboratory testing

All samples are tested using routinely used nucleic acid amplification tests (NAAT) for the presence of CT (Table 1). The frozen samples from participants testing CT positive by routine NAAT are further tested for viability with viability polymerase chain reaction (vPCR; unpublished protocol, [name], [name], [name], [name], Medical Microbiology, MUMC, Maastricht) directed at the detection of DNA inside intact microbial cells or with culture [45]. A positive culture or vPCR result implies the presence of viable and infectious CT and provides information on the potential clinical relevance of the infection. Other non-routine measures include the CT-DNA load that will be assessed using quantitative NAAT. The CT genotype will be determined using high resolution multilocus sequence typing (hr-MLST) [46]. Strain typing is here specifically used to confirm self-infection or persistence. A selection of samples is tested for Y chromosome DNA as a marker for semen exposure to assess underreporting of sexual behaviour [47].

### Collection of self-reported data

Data will be collected by online self-administered questionnaires at inclusion, and during follow-up around the sampling times. The questionnaire at inclusion contains questions on age, ethnicity, gender, socio-economic status. All questionnaires contain questions on number of partners, and for each sexual partner the sexual behaviour (genital, anal, oral sex) in the past two weeks, testing for STI and treatment. It also includes questions on behaviours such as contraceptive use, antibiotic use, drug use, STI testing during follow-up, and on list of symptoms. Further, participant data will be collected concerning treatment type and compliance. For the purpose of process evaluation, a few questions are included that address acceptability and possible difficulties encountered related to the participation in the study. Each participant has a study code under which all data (samples and questionnaires) are collected and analysed.

### Outcome in analyses

Detection of anorectal and genital CT by NAAT (primary outcome), viability and load (secondary outcomes).

### Definition of transmission

Transmission is defined as an observed incident CT detection post-treatment (a) after having sex with a source partner (by self-reported behaviour and biomarker-validation), and (b) when another anatomical source location tested positive, i.e., self-infection. In such cases, self-infection is considered likely when CT strain types do not differ between anatomic sites of a woman. Samples with CT detection that follow a sample with CT detection may represent persistence and are considered not indicative for transmission. In such cases, persistence is considered likely when CT strain types do not differ in a woman over time.

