### Defining sexual exposure

In women, the process of CT acquisition from an infected partner, i.e., via sex, is defined based on sexual behaviour data from the detailed and frequent questionnaires and by biomarker assessment. The actual CT status of the partner during follow-up will in most cases be unknown. Hence, the sexual behaviour that is reported during follow-up may also include sex with CT negative partners. The risk estimate for the association between sexual exposure and incident CT detection reflects the risk of transmission given this sexual practice and regardless of the partner's CT status. This will be a good proxy to the actual transmission probability for a given sexual practice in ‘real life’ and is most relevant in the practical care setting where information on sexual behaviour is routinely asked about and registered and partners’ CT status is often lacking. To validate sexual exposure from a man, especially to indicate underreporting, biomarker validation is applied.

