### Defining alternate anatomic site exposure

The process of CT anorectal acquisition from her own genital CT infection and vice versa is defined based on the CT test results. Exposure is defined as presence of CT detection at the other anatomic site at the same sampling moment and/or the previous sampling moment. CT typing results are also used to confirm the link between the two detections.

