	Sexual exposure and genital site exposure	Anorectal sexual exposure (at T_x_) AND genital CT positive (at T_x_ and/or T_x-2_)	Sexual transmission AND/OR Transmission from genital site

^a^Based on self-administered questionnaires and semen biomarker assessment

^b^T_x:_ test result at the sampling; T_x-2:_ test result at the sampling two weeks earlier

^c^Strain typing is used to further aid interpretation of the observed positive CT test result, specifically to confirm self-infection (i.e., strain types do not differ between anatomic sites) or persistence (i.e., strain types do not differ over time)

Risks will be expressed by odds ratio‘s and 95 % confidence intervals. Co-factors (such as age, but also treatment-type) will be included in the models to account for their potential role as a confounding factor or effect-modifier in the associations between exposure and CT detection. Also, these co-factors are assessed for their association with CT detection.

Sensitivity analyses will be undertaken by varying the definition of the outcome (primary and secondary outcomes) and by varying the definition of the sexual exposure (e.g., including and excluding sexual practices). By performing a (limited) process evaluation of our study, we will obtain insights in the factors that have affected participation and possible loss-to-follow-up.

In a sub analysis, in which the unit of analysis will be an individual woman (not the 2-week episodes), a head-to-head comparison of the two treatments will be conducted.

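### Matching strain types are read as confirming self-infection or persistence, but reinfection by the same partner can give the same match, and a consecutive positive with a changed type is left unclassified

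*Protocol article*

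**What the plan says.** Four sections of the protocol article give typing a role in attribution.

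- *Definition of transmission*, between sites: "self-infection is considered likely when CT strain types do not differ between anatomic sites of a woman". Over time: "persistence is considered likely when CT strain types do not differ in a woman over time".
- *Laboratory testing* is firmer: "Strain typing is here specifically used to confirm self-infection or persistence".
- *Defining alternate anatomic site exposure*: "CT typing results are also used to confirm the link between the two detections".
- *Statistical analyses*, Table 2 footnote c, says typing helps to interpret a positive result, "specifically to confirm self-infection (i.e., strain types do not differ between anatomic sites) or persistence".

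None of these rules makes an exception for a woman who had sex in the interval. *Defining sexual exposure* concedes: "The actual CT status of the partner during follow-up will in most cases be unknown".

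On consecutive positives, *Definition of transmission* says: "Samples with CT detection that follow a sample with CT detection may represent persistence and are considered not indicative for transmission". That sentence carries no strain condition. The sentence after it applies typing only to the case where the types agree.

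**The concern.** A strain match is strong evidence for a route only if the rival routes would seldom produce one. The main rival here is reinfection by a partner who shares the woman's earlier strain and is still infected. Such a partner can return that strain to one or both sites. Across sites the result looks like self-infection; over time it looks like persistence. The article does not mention this rival, and *Limitations* covers misclassification only through under-reported sex and clearance before sampling.

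The study aims to separate transmission from male partners from transmission between a woman's own sites. The rule as written can credit sexual reinfection to self-infection or persistence.

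The rule for consecutive positives raises a second problem. A changed type is evidence of a new infection, yet read literally the sample is not transmission, and no other class is given for it.

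**Working it through.** The plan gives no figure on this point, so there is none to reproduce. The check sets the rules side by side and then asks how much a match can tell.

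**1. What each result can show**

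| Process | Same type expected? |
|---|---|
| Self-infection between sites | Yes |
| Persistence over time | Yes |
| Reinfection by a partner carrying the woman's earlier strain | Usually |
| Infection from another source | Only by chance |

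A mismatch argues against the first two rows. A match does not separate them from the third. Typing refutes better than it confirms.

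**2. Where this applies**

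In Table 2, model 2, the site-exposure-only category excludes reported sex at the outcome site, not all sex. The double-exposure category leaves the two routes open. Footnote c then brings in typing to confirm self-infection, which is the step that cannot separate the routes when there was sex. Alternate-site exposure also includes positivity at the same sampling moment. One partner reinfecting both sites in one interval would therefore produce both alternate-site exposure and matching types.

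**3. How much a match adds**

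Inputs, all assumed because the document gives none:

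- s: prior probability that the detection is self-infection rather than sexual acquisition
- q: share of sexual acquisitions that carry the woman's earlier strain
- m: chance match among the other sexual acquisitions, taken as 0.05 to 0.30
- self-infection always gives a match

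Formula: P(self-infection | match) = s / [s + (1 − s)(q + (1 − q)m)]

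With s = 0.5:

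- q = 0, m = 0.05: 0.5 / (0.5 + 0.5 × 0.05) = 0.95; m = 0.30: 0.5 / (0.5 + 0.5 × 0.30) = 0.77
- q = 0.5, m = 0.05: 0.5 / (0.5 + 0.5 × 0.525) = 0.66; m = 0.30: 0.5 / (0.5 + 0.5 × 0.65) = 0.61
- q = 1, any m: 0.5 / (0.5 + 0.5 × 1) = 0.50

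Other priors, from m = 0.30 to m = 0.05:

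| s | q = 0 | q = 0.5 | q = 1 |
|---|---|---|---|
| 0.25 | 0.53–0.87 | 0.34–0.39 | 0.25 |
| 0.50 | 0.77–0.95 | 0.61–0.66 | 0.50 |
| 0.75 | 0.91–0.98 | 0.82–0.85 | 0.75 |

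At q = 1 a match leaves the prior unchanged. The same formula serves for persistence, with s as its prior.

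**4. Consecutive positives**

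The blanket sentence keeps every positive after a positive out of transmission. The strain sentence makes persistence likely only if the types agree. Together they leave the discordant case as neither transmission nor likely persistence.

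**The case against.** The main analysis does not classify by strain. Both Table 2 models are built from sexual exposure and NAAT results at the other site, and typing enters only as an aid to interpretation. Table 1 shows that MLST is done in a subset. *Definition of transmission* says only that the routes are likely. Model 2 separates site exposure without reported sex at that site from double exposure, and reads the latter as either route or both. Sexual exposure is checked by biomarker, and questionnaires ask about each partner's testing and treatment. All of this stands and limits the reach of the point. It does not remove the point, because three other places say typing confirms, and no rule uses the partner data to qualify a match.

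Four stronger readings are tempting, and the document does not support them:

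- **A match carries no information.** That holds only at q = 1. A new partner with a different strain would usually give a mismatch. The 75% expected to be positive at both sites at inclusion is co-positivity, not strain concordance.
- **Discordant consecutive positives are thrown away.** The text does not say so. It leaves their class unstated.
- **The Table 2 odds ratios are shifted towards self-infection by the strain rule.** They contain no strain term.
- **The consecutive-positive rule inflates self-infection.** It takes such samples out of transmission altogether, and the article's definition of transmission includes self-infection. No net direction is shown.

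**Conclusion.** The point holds in a limited form. In intervals with sexual exposure, reported or under-reported, matching types are compatible with self-infection or persistence but do not confirm either. At a prior of 0.5, the probability of self-infection given a match runs from 0.95 down to 0.50, depending mainly on the share of same-strain reinfection, which the study cannot observe directly while partners' status is mostly unknown. These figures rest on assumed s, q and m and on self-infection always producing a match; typing error or mixed infection would weaken that last assumption. They illustrate the range and do not estimate it.

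The handling of a consecutive positive with a changed type is a gap in the rule as written. Both problems affect how detections in the typed subset are attributed and described. No sample-size figure changes in a computable way.

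**What to change.** Reword *Laboratory testing*, *Definition of transmission*, *Defining alternate anatomic site exposure* and Table 2 footnote c as follows.

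1. Discordant types count as evidence against self-infection or persistence.
2. Concordant types are compatible with, and do not confirm, these routes when any sex was reported in the interval or Y-chromosomal DNA was found where tested.
3. Split those episodes with the per-partner data already planned (behaviour, STI testing, treatment). Report the rest as indeterminate between self-infection or persistence and same-partner reinfection.
4. Where typing is available, class a consecutive positive with a different type as a new, incident detection.

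The fix uses questionnaire and typing data already planned. A negative Y-DNA result should not be required for every likely label: the assay is run on a selection of samples, so this could mean more testing, and *Strengths* acknowledges that it may miss exposures, so a negative cannot exclude sex. The cost is some rewording and more detections reported as indeterminate.

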Two knowledge gaps can be identified in the evidence for CT control strategies. First, we do not understand the role of anorectal CT in women in overall CT spread. In women, anorectal infections are about as common as genital infections, with proportions positive ranging between 7 - 27 % of anorectally tested women [13-25]. Yet, most anorectal CT infections remain undetected as general practitioners, hospital and population testing initiatives ignore anorectal CT and largely focus on genital CT [26]. STI clinics do test women at the anorectal site on indication, i.e., when they report anal sex or symptoms. Still, with half of all anorectal CT occurring in women who do not report anal sex, many anorectal infections are left untested. Second, we do not know whether transmission of CT can occur in the weeks following currently recommended treatment. Prior studies have shown considerable detection of both anorectal and genital CT after treatment in women and men [27–32]. Detection rates depended on the number of samples taken and type of tests used, demonstrating up to 40 % of treated cases having at least one positive sample when sampled multiple times within 8 weeks [27]. Indeed, repeat genital CT infections are common following treatment, varying between 10 % and 30 % when re-testing CT positive treated women between 3 months and a year later [33]. Guidelines advise such re-screening at 3 months after a CT diagnosis. Yet, in practice, re-screening occurs in less than a third of patients in the Netherlands [34]. Current care does not include a routine re-test of patients within 3 months of treatment [35-37] nor does it include an anorectal re-test 3 months after the genital CT treatment. Many uncertainties exist on the clinical relevance of a post-treatment CT detection. It is unknown whether it reflects transmission after sexual exposure or self-infection. It is also unknown whether detection of CT nucleic acids indicates viable or nonviable CT and what organism loads are present [38]. Suboptimal treatment may possibly play a role, but evidence is inconclusive leading to considerable debate on this issue [39–42].

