### Study population

The eligible study population is likely to reflect the current STI clinic populations. Eligible are heterosexual women with symptomatic or asymptomatic genital and/or anorectal CT infection, who are not pregnant and 18 years or older. Exclusion criteria are recent reported use of antibiotics, HIV positivity, syphilis and infection with *Neisseria gonorrhoea*. As single anorectal CT is uncommon and around 75-95 % of genital CT positive women also have anorectal CT [13–25], it is expected that of the included women only few will have anorectal CT only. The majority (75 %) expectedly will have anorectal CT in combination with genital CT, and most of the remainder will have genital CT only at inclusion in the study. Treatment occurs according to regular care and international guidelines [35–37]. Women who are anorectally tested in routine care and found anorectal CT positive are treated with a 7-day course of doxycycline 100 mg twice daily with the first dosis being directly observed. All other women receive a directly observed single dose of azithromycin 1000 mg [35–37]; these women tested genitally CT positive in routine care and were either anorectally untested in routine care or were tested anorectally CT negative.

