### Statistical analyses

The main study questions will be answered by analysing the data on the level of episodes. For each incident CT detection, the information of the preceding sample results, and the sexual behaviour information from the preceding 2-week interval, is analysed. Using mixed models, univariate and multivariate logistic regression analyses will be applied to calculate rates of incident CT anorectal and genital detection, controlling for repeated measurements in a person. Thereby, the relative contributions are assessed of sexual exposure and of alternate anatomic site exposure, i.e., sexual transmission and self-infection. This will be done by including different exposures as co-factors and this will also be done comparing categories of sexual exposure, anatomic site exposure, and both exposures compared to no such exposure (see Table 2).

**Table 2 Tab2:** Main regression models in FemCure study

	Exposure categories	Definition in the data^b^	Interpretation^c^ of positive CT test result
Outcome incident genital CT detection			
Model 1	Sexual exposure^a^	Genital sexual exposure (at T_x_)	
	Alternate site exposure	Anorectal CT positive (at T_x_ and/or T_x-2_)	
Model 2	No exposure	No genital sexual exposure (at T_x_) AND anorectal CT negative (at T_x_ and T_x-2_)	Persistence
	Genital sexual exposure only	Genital sexual exposure (at T_x_) AND anorectal CT negative (at T_x_ and T_x-2_)	Sexual transmission
	Anorectal site exposure only	No genital sexual exposure (at T_x_) AND anorectal CT positive (at T_x_ and/or T_x-2_)	Transmission from anorectal site
	Sexual exposure and anorectal site exposure	Genital sexual exposure (at T_x_) AND anorectal CT positive (at T_x_ and/or T_x-2_)	Sexual transmission AND/OR Transmission from anorectal site
Outcome incident anorectal CT detection			
Model 1	Sexual exposure^a^	Anorectal sexual exposure (at T_x_)	
	Alternate site exposure	Genital CT positive (at T_x_ and/or T_x-2_)	
Model 2	No exposure	No anorectal sexual exposure (at T_x_) AND genital CT negative (at T_x_ and T_x-2_)	Persistence
	Anorectal sexual exposure only	Anorectal sexual exposure (at T_x_) AND genital CT negative (at T_x_ and T_x-2_)	Sexual transmission
	Genital site exposure only	No anorectal sexual exposure (at T_x_) AND genital CT positive (at T_x_ and/or T_x-2_)	Transmission from genital site

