### Numbers and power

Based on the power calculations we need to include 300 - 380 women with full retention, to be able to answer the main study question and the sub-analyses with sufficient power (at least 70 %) to show statistically significant (5 %) associations of a relevant size. This was calculated in different scenarios by varying the assumptions in number of women with full data (300–380), the percentage of CT detections (15-30 %), the percentage of reported sex during a 2-week episode (20-60 %) and the percentage of alternate anatomic site exposure (10-30 %). Accounting for women who are anorectally CT negative at inclusion, loss-to-follow up, missing data, and persistence, we need to recruit 400 women in the study to be able to have sufficient numbers of samples that can be analysed.

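### One negative NAAT turns a site infected before treatment into a site at risk of incident detection, so the self-infection estimate cannot be told apart from residual infection

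*Protocol article*

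**What the plan says.** Under *Definition of transmission*, transmission is an incident detection after treatment, following sex or with the other site positive. The only detections set aside are those directly preceded by a detection: "Samples with CT detection that follow a sample with CT detection may represent persistence and are considered not indicative for transmission". The article gives no other definition of incident.

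Under *Defining alternate anatomic site exposure*: "Exposure is defined as presence of CT detection at the other anatomic site at the same sampling moment and/or the previous sampling moment". Table 2 builds its cells from the same two swabs. For the genital outcome, the cell read as transmission from the anorectal site is "No genital sexual exposure (at T_x_) AND anorectal CT positive (at T_x_ and/or T_x-2"). The anorectal outcome mirrors this. An incident positive with neither exposure is read as persistence.

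No cell, stratum or named covariate refers to the T0 status of the outcome site. The covariate sentence reads: "Co-factors (such as age, but also treatment-type) will be included in the models". Under *Study population*: "The majority (75 %) expectedly will have anorectal CT in combination with genital CT". The *Background* cites earlier work "demonstrating up to 40 % of treated cases having at least one positive sample when sampled multiple times within 8 weeks". NAAT detection is the primary outcome; viability and load are secondary.

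**The concern.** For most women the outcome site was infected at T0 and has just been treated. A positive there after one negative can be a new infection, or the old one detected intermittently. The plan accepts the second reading when the other site is negative, since Table 2 then says persistence. When the other site is positive, the same event becomes transmission from that site.

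If residual detection tends to occur at both sites of the same woman, or is commoner at both sites early after treatment, residual positives gather in the exposed cell. That association is the study's self-infection estimate, and it is meant to inform recommendations on anorectal testing and treatment.

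**Working it through.** The plan states no expected odds ratio or number of incident detections, so there is no figure of its own to reproduce. The sample-size range does not bear on this point.

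**1. Who is at risk.** Dual infection at T0: 0.75 × 400 = 300 women. The other 100 are split here, by assumption, into 22% genital only (88) and 3% anorectal only (12). The outcome site was infected at T0 in 300 + 88 = 388 women for the genital outcome and 300 + 12 = 312 for the anorectal outcome. Clean at T0: 12 genital and 88 anorectal sites (100 anorectal if nobody is anorectal only).

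**2. One woman traced through the rules.** Both sites are positive at T0 with one strain, and she reports no sex. Her anorectal swab is negative at week 2 and positive at week 4; her genital swab is positive at week 2. The week 4 anorectal positive does not follow a positive, so it is incident. The genital site was positive at the previous visit, so Table 2 reads transmission from the genital site. With genital swabs negative at weeks 2 and 4, the same event is read as persistence. Typing does not decide: the strain matches between sites (self-infection) and over time (persistence), and no precedence is given.

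**3. False incident detections per residually positive site.** Take a site infected at T0, swabbed at weeks 1, 2, 4, 6 and 8, with detection probability *p* per swab and no reinfection.
- One-negative rule: 4*p*(1−*p*). At *p* = 0.5 this is 1.00; at *p* = 0.8 it is 0.64.
- Two-negative rule: 3*p*(1−*p*)². At *p* = 0.5 this is 0.38; at *p* = 0.8 it is 0.10.

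**4. Effect on the odds ratio.** Simulation with no transmission: 400 women, T0 mix as in step 1, swabs at weeks 1, 2, 4, 6, 8, 10 and 12. Residual positives occur only at T0-infected sites, calibrated to about 40% of women with any positive by week 8. The model is a random-intercept logistic Model 1 (alternate-site and sexual exposure), with 60 replicates per scenario. Decay (logit per week) and the woman-level SD are assumptions. Entries are the median alternate-site odds ratio, with the false rejection rate at 5%.

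| Decay, SD | Genital | Anorectal |
|---|---|---|
| 0.35, 0 | 2.01 (40%) | 1.30 (15%) |
| 0.2, 0 | 1.40 (7%) | 0.98 (5%) |
| 0, 1 | 1.92 (68%) | 1.45 (23%) |
| 0.2, 1 | 2.38 (75%) | 1.86 (50%) |
| 0.35, 1 | 3.43 (87%) | 2.35 (63%) |

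Every false event arose at a T0-infected site: 61-139 genital and 48-112 anorectal per study. With no decay and no shared effect (45% with any positive by week 8) the odds ratios were 0.94 and 0.73, so there was no inflation.

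**5. Crude comparison.** Separate assumptions: genital CT in all women and anorectal CT in 75% at T0, 2% new detection per visit and site, 5-15% of women shedding at all their T0-positive sites to week 8, 40-80% detection per swab, exposure at the previous visit only. The crude anorectal odds ratio is about 4.4-9.8 pooled, 5.8-23 in T0-positive women and about 1 in T0-negative women. With shedding independent between sites, the pooled figure is 1.0-1.1.

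**6. What the remedies achieve.**
- T0-clean sites: no false events in any step 4 scenario.
- Two negatives: false events fall to 28-100 (genital) and 23-80 (anorectal), but the odds ratio stays at 1.5-3.5 and 1.2-3.4.
- Time since treatment removes only the decay part. In exploratory runs with more detection, the genital odds ratio fell from 2.34 to 0.97 with decay only, and from 3.33 to 1.67 with decay plus SD 1.
- Precision: with 80-100 women (woman as unit), 30% exposed and 70% power, the detectable odds ratio is about 3.1-4.9. Under step 5, the T0-negative anorectal stratum has about 12 events per 400 women, of which 0.4-1.4 are exposed.

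**The case against.** The strongest objection is that correlation between sites is assumed. No passage says that residual DNA occurs at both sites of the same woman, and without shared load or common decay the inflation vanishes. That stands, and it makes the size conditional. The labelling problem in steps 2 and 3 does not need the correlation.

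The plan also has safeguards: strain typing, viability and load as secondary outcomes, and sensitivity analyses that vary the outcome. They help but do not close the gap. Typing is done in a subset and cannot separate one strain present at both sites since T0. Viability is measured after treatment only at weeks 4, 8 and 12, and a viable organism may itself be a persisting one.

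The wording is also looser than a strict rule. Positive after positive *may* be persistence, the covariates are given as examples, and a fuller protocol may define incident. T0 status is thus unnamed rather than excluded, and the Table 2 persistence label extends the definition rather than formally contradicting it. But the article itself fixes the reading of each Table 2 cell, and that reading needs a T0 condition.

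Two stronger readings are tempting and fail. One is that pooling T0-clean with T0-infected sites causes the bias. It dilutes it: in the last scenario of the table the anorectal odds ratio is 2.35 pooled and 3.98 in T0-infected sites. The other comes from *Numbers and power*: "Accounting for women who are anorectally CT negative at inclusion". A reader might infer that these women are written off for the incident anorectal outcome. The sentence says only that the recruitment target allows for them; they may be counted there for other reasons, such as contributing less anorectal exposure to the genital models.

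**Conclusion.** The point holds as a defect of definition and interpretation. As written, a reappearance after one negative NAAT at a T0-infected site is incident and, with the other site positive and no relevant sex, is read as transmission from that site. A raised self-infection odds ratio would not show that self-infection occurred.

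The size depends on correlated residual detection. Under the step 4 assumptions the spurious odds ratio is about 1.0-2.4 (anorectal) and 1.4-3.4 (genital) in the random-intercept model. The crude figures are larger but are not from the mixed model that the plan specifies. A reader might infer that the self-infection estimate is certain to be biased. The documents do not support that, because they are silent on whether residual detection is correlated between sites.

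**What to change.** In *Definition of transmission* and *Statistical analyses* (with Table 2):

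1. Define incident detection explicitly. Report the number of incident detections and the alternate-site odds ratio separately by T0 NAAT status of the outcome site.
2. Add time since treatment to the models.
3. For T0-infected sites, label an alternate-site-exposed incident detection *self-infection or persistence* when the strain matches both T0 and the other site, or when it is untyped.
4. Use two consecutive negatives at T0-infected sites, and the viability results at weeks 4, 8 and 12, as sensitivity analyses only.

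The change is to analysis wording: swabs from both sites at T0 are already collected and tested by NAAT. The two-negative rule removes about 14-16% of at-risk episodes (weeks 2-12, simulated under step 5).

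The real cost is precision. The T0-negative anorectal stratum, about 88-100 women with few exposed events, will give wide intervals. The T0-negative genital stratum (about 12 women if 3% are anorectal only) is too small to estimate, so the genital self-infection result has to be reported as not separable from persistence.
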